#### Interventions: Concomitant care, modifications and adverse effects

PNE plus NMS or NMS alone will be implemented without altering the usual care pathways, including medication use, which will continue for both trial arms. The protocol of this study is conservative, and both interventions (PNE and NMS) are low risk [29,30]. However, if patients in the intervention group report severe adverse events (e.g., fainting or dizziness), mild side effects (e.g., physical or mental), or experience severe worsening of their clinical condition (e.g., presenting in a session with a VAS ranging from 8 to 10), they will discontinue the study and be referred for additional treatment to a physician.

The physiotherapist administering the treatment will monitor any adverse events or worsening of the patient’s clinical condition during each session. If any adverse events are present, the principal investigator will be informed, and a weekly list will be compiled to monitor them. Moreover, patients will be instructed to return to the principal investigator if they experience any back pain or adverse effects after the trial. Participants may choose to stop participating in the intervention or study for any reason. They will be informed about the permission, consent, and assent forms, and they can choose to stop participating in the study at any time without any consequences.

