## Methods

### Study design

This study will be a single-blind assessor randomized clinical trial (RCT) with two arms (group 1: Experimental-PNE plus NMS; group 2: Control-NMS) comparing the outcomes between intervention groups in patients with CLBP. The Standard Protocol Items: Recommendations for Interventional Trials (SPIRIT) reporting guidelines are used to report this protocol [33,34] and are presented in S1 File. This study will follow the Consolidated Standards of Reporting Trials guidelines (CONSORT) for RCT [35]. The interventions will be presented following the Template for Intervention Description and Replication (TIDieR) checklist [36] reported in S2 File. A study flowchart is presented in Table 1 and Fig 1 [37].

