#### Inclusion criteria

We will include participants who satisfy the following criteria: (a) Persian-native speaker (male and female); (b) presenting CLBP diagnosed by an experienced physiotherapist; (c) with complaints of more than 3 months; (d) with a pain intensity of LBP ≥ 5 on the Visual Analog Scale (VAS) [39]; and (e) with a pattern reported between the lower ribs and the creased part of the buttocks without nonspecific pathoanatomical cause [32].

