### Interventions

The groups will receive different treatment programs as follows:

In Group 1 Experimental-PNE plus NMS, the intervention will be offered three days a week for up to 8 weeks;In Group 2 Control–NMS, the intervention will be administered three days a week for up to 8 weeks.

The interventions will be delivered face-to-face in an exercise room of a physical therapy clinic. Each session will be provided individually by a physical therapist with an average of 5 years of experience in musculoskeletal pain.

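### Patients who worsen or have side effects leave the study, not just treatment, and are then analysed at the mean of those who stayed

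*Protocol article*

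**What the plan says.** Under Interventions: Concomitant care, modifications and adverse effects, the removal rule opens with "However, if patients in the intervention group report severe adverse events". It adds mild physical or mental side effects as a trigger and ends with "severe worsening of their clinical condition (e.g., presenting in a session with a VAS ranging from 8 to 10), they will discontinue the study". These patients will also "be referred for additional treatment to a physician".

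The next paragraph of that section says "Participants may choose to stop participating in the intervention or study for any reason", so the authors do distinguish the two kinds of stopping. Nothing in the article says that outcomes are still collected after removal.

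Three other places matter:

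- **Statistical analysis:** for the intention-to-treat analysis, missing post-test values are replaced by group means.
- **Adherence:** everyone randomised is to be analysed, treated or not. Sensitivity analyses are to be done only as needed.
- **Inclusion criteria:** entry requires a VAS of at least 5, with no upper limit.

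**The concern.** The worsening trigger is read on the scale of the primary outcome, so a value missing for this reason is informative: it is missing because pain was high. Replacing it with the mean of patients who stayed turns a probable poor result into an average one. The rule also removes patients for reasons that justify stopping treatment but not stopping measurement.

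Two points of wording make the effect hard to predict:

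- **No baseline reference.** Severe worsening is illustrated by a VAS of 8 to 10, yet a patient may enter the trial at 8.
- **Arm covered.** The rule names the intervention group. The same section says that usual care is something "which will continue for both trial arms", and Study design speaks of "comparing the outcomes between intervention groups in patients with CLBP". Both favour a two-arm reading, but no sentence settles it.

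Removal for mild side effects loses data needlessly. Those patients need not have poor pain outcomes, so no bias is claimed for them. The general weakness of group-mean imputation for other dropout is a separate matter.

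**Working it through.** The plan states no figure to reproduce. The size was estimated by arithmetic and simulation.

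**From the article:** 30 patients per arm; entry at VAS 5 or more; VAS range 0–10; MCID 1.5 cm; 8 weeks of treatment; missing post-test values set to the group mean.

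**Assumed, because the article gives no pain distributions:**

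- Latent baseline mean and SD of (6.0, 1.5), (6.5, 1.5) or (6.5, 1.8), with 60% of the variance between persons.
- A mean fall of 2 cm over 8 weeks, with a between-patient SD of that change of 1.0 or 2.0 cm.
- Removal at a weekly check in weeks 1–7 if VAS is at least 8 and has risen by at least 1.5 cm (the MCID) or 3 cm (twice the MCID) from baseline.
- Group mean taken as the week-8 mean of remaining patients in the same arm; t-test on change.

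**Mechanism.** Let p be the share of an arm removed and g the gap between the week-8 VAS that removed patients would have had and the mean of those who stayed. The arm mean is then too favourable by p × g. The treatment difference is biased by the difference of these products between arms.

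**Both arms covered, no effect.** The two products cancel: absolute bias is at most 0.004 cm.

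**Both arms covered, extra fall of 1.5 cm with PNE+NMS** (full-data difference 1.39–1.48 cm after bounding). More control patients are removed and given better values, so the effect is understated:

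| SD of change | Baseline mean, SD | Removed, rise 1.5 cm (PNE+NMS v control) | Understated (cm) | Removed, rise 3 cm | Understated (cm) |
|---|---|---|---|---|---|
| 1.0 | 6.0, 1.5 | 3.1% v 6.7% | 0.058 | 0.3% v 0.7% | 0.007 |
| 1.0 | 6.5, 1.5 | 4.4% v 8.9% | 0.066 | 0.3% v 0.9% | 0.008 |
| 1.0 | 6.5, 1.8 | 8.4% v 14.6% | 0.078 | 1.2% v 2.5% | 0.014 |
| 2.0 | 6.0, 1.5 | 5.0% v 11.1% | 0.185 | 0.7% v 2.2% | 0.052 |
| 2.0 | 6.5, 1.5 | 6.5% v 13.5% | 0.189 | 0.8% v 2.4% | 0.048 |
| 2.0 | 6.5, 1.8 | 10.5% v 18.4% | 0.186 | 1.9% v 4.1% | 0.053 |

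That is about 4–13% of the effect with a 1.5 cm rise and 0.5–4% with a 3 cm rise.

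**PNE+NMS only, no effect.** With a 1.5 cm rise, 6.7–18.4% of that arm are removed, the bias in its favour is 0.10–0.42 cm, and type I error is 6–13%. With a 3 cm rise the figures are 0.7–4.2%, 0.01–0.10 cm and 5–6%. As a check on the mechanism, a bias of 0.33 cm with 11.1% removed implies g = 0.33 / 0.111 ≈ 3.0 cm.

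**Effect of referral.** The figures above assume that removed patients stay on their treatment course.

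- If referral lowers their week-8 VAS by 1 cm, the both-arm understatement is 0.001–0.13 cm and the one-arm bias 0.001–0.23 cm.
- If it lowers it by 2 cm, the both-arm result runs from 0.05 cm overstated to 0.06 cm understated. With a 1.5 cm rise, the one-arm result runs from 0.11 cm in favour of PNE+NMS to 0.12 cm against it.

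**Frequency of checks.** Treatment is given three times a week. With 23 session checks and independent noise (an upper case, since nearby sessions are likely to be correlated), the both-arm understatement is 0.09–0.27 cm (1.5 cm rise) or 0.01–0.09 cm (3 cm rise).

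**Literal use of 8–10.** If staff acted on VAS 8 or more alone, with no rise required, weekly checks would remove 18–42% of control patients. The both-arm understatement would be roughly 0.14–0.4 cm. This is an extreme reading, but the article gives no other number.

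**The case against.** - **It may be loose wording.** The rule stands under a heading about interventions, the intention-to-treat statement fits a stop-treatment reading, and the full protocol may provide for follow-up. This is possible. But the article itself separates stopping the intervention from stopping the study, and the rule names the study. If only treatment was meant, the sentence still needs correcting.
- **The effect is small and conservative.** This stands for the two-arm reading. The 3 cm rise is nearer to severe worsening than the MCID is, and it gives at most 0.05 cm with weekly checks. Because removed patients are referred for treatment, even the direction is not certain.
- **The one-arm case is unlikely, and much of its type I error has another source.** The text does favour both arms. With both arms covered, no effect and a 1.5 cm rise, type I error is already about 6–10%, because mean imputation shrinks the variance. That cost belongs to the imputation method, so the type I figures should carry little weight here.
- **Sensitivity analyses could help.** Worst-case values, or the session VAS that triggered removal, could bound the result. They would be assumptions in place of week-8 and 6-month data that could have been collected.
- **Worsening already implies an earlier state.** This is fair, and 8–10 is only an example. Without a reference point or an amount, though, staff must decide case by case.

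**Conclusion.** The point holds as a minor design fault. Followed as written, the removal rule and the imputation rule together analyse patients who left because of high pain as if they had average pain, which defeats the intention-to-treat aim for those patients.

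Under the two-arm reading there is no bias under no effect, and with weekly checks a true 1.5 cm effect is understated by about 0.01–0.19 cm. Bias in favour of PNE+NMS arises if the rule is applied to that arm alone. All sizes depend on assumed pain distributions, an assumed definition of severe worsening and an assumed course after referral; effective referral could remove or reverse the bias. The case for changing the rule is that the loss is avoidable and a later analysis plan cannot undo it, not that a large bias has been shown.

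**What to change.** Amend the rule so that these events stop or pause the intervention and trigger referral, in either arm, without ending follow-up. Collect the 8-week and 6-month questionnaires unless the patient withdraws consent, and analyse the observed values as randomised. Ask the clinical team to define severe worsening relative to baseline and to reconsider whether a mild side effect should be a trigger. Referral for high pain stays as it is; no threshold is proposed here.

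The cost is a short amendment, an instruction to staff, and questionnaires from a few patients who have stopped treatment. Outcomes are self-assessed, so the burden is small. The Trial status section says recruitment is under way, so the change should be made soon: outcomes not collected at their due time cannot be recovered.

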#### Outcomes variables

Data will be self-assessed at three measurement time points: before the intervention, after 8 weeks of intervention, and at 6 months follow-up. A researcher blinded to the group allocation will collect, share, and maintain confidentiality before, during, and after the trial, ensuring the privacy of all personal information about potential and enrolled participants and outcomes. Unblinding and the procedure for revealing a participant’s allocated intervention during the trial will only be permissible in case of adverse events.

#### Initial socio-demographic and clinical characteristics of patients

The patients’ demographics and clinical characteristics will be collected at baseline as follows: age, weight, height, body mass index (BMI), radiographic score, marital status or living with a partner, educational level, employment status, duration of symptoms, VAS, disability, number of daily medications used, time of onset of severe back pain, joint replacements, and the number and name of other diseases.

#### Outcomes measures

The primary outcome will be pain intensity [30]. The secondary outcomes will be disability [23], fear-avoidance beliefs during work and physical activity [32], self-efficacy [32], and fear of movement [30].

### Primary outcome

#### Pain

The VAS is an extensively used psychometric response scale that assesses participants’ pain severity. It requires participants to rate their pain severity along a horizontal line with ten points, with 0 and an image of a smiling face indicate no pain, and 10 and an image of pain and discomfort indicate severe pain. The VAS has demonstrated excellent reliability and validity, with a high internal consistency of ICC = 0.91 [23]. The minimal clinically important difference (MCID) for people with CLBP is 1.5 cm, as reported in a previous study [56].

### Secondary outcomes measurements

#### Disability

The Persian version of the Oswestry questionnaire will be used to examine the degree of disability in participants with CLBP [57]. This questionnaire consists of 10 six-option items that assess an individual’s capacity to perform daily activities. Each item assigns a disability score to the activity, ranging from zero (no pain during the desired function) to five (severe pain prevents performance). The Oswestry Disability Index is the sum of the scores of these ten items, multiplied by two, producing a value between 0 and 100. A zero score indicates that a person can perform daily activities without pain. Scores between 1 and 20 indicate mild or minor disability, 21 to 40 indicate moderate disability, 41 to 60 indicate severe disability, and 61 to 80 indicate a debilitating disability. Scores of 81 and higher indicate that a person is bed-bound or exaggerating symptoms. The validity of the Oswestry questionnaire has been confirmed with a Cronbach’s alpha of 75%, and its reliability has been reported with a correlation coefficient of 0.92 [58]. The lowest MCID in individuals with CLBP is 10 points [59].

#### Fear-avoidance beliefs

The Persian version of the Fear-Avoidance Beliefs Questionnaire (FABQ) [60] will be used to assess patients’ fear-avoidance beliefs during physical activity and work. It consists of 16 items related to physical activity (FABQ-PA) and work (FABQ-W) that affect patients with LBP. For FABQ-W, those scoring 34 or higher out of a possible 42 points are less likely to return to work within four weeks. In contrast, a score of 15 out of 24 points on the FABQ-PA indicates fear-avoidance beliefs regarding the physical activities [60]. The Persian version of the FABQ has demonstrated validity and reliability (ICC = 0.80) for measuring fear-avoidance beliefs in patients with CLBP [60]. A variation of 4 points for FABQ-PA and 7 points for FABQ-W represents the MCID in CLBP [61].

#### Self-efficacy

The Persian version of the Pain Self-Efficacy Questionnaire (PSEQ) [62] will be used to assess self-efficacy. The questionnaire is a valid and reliable measure of pain self-efficacy beliefs (ICC = 0.92) [62]. The PSEQ is a 10-item questionnaire ranging from 0 to 60 that assesses patients’ confidence in their ability to perform a range of activities despite pain. For example, it includes items such as: “I can do most of the household chores (e.g., tidying up, washing dishes), despite the pain”, and “I can gradually increase my activity level, despite the pain. Lower PSEQ scores indicate lower confidence levels. The MCID for PSQE is 9 points [63].

#### Fear of movement

The Tampa Scale of Kinesiophobia (TSK) measures fear of movement or kinesiophobia in patients with LBP [64]. The total score on this scale ranges from 17 to 68, with 68 indicating severe fear of movement, 37 indicating fear of movement, and 17 indicating no fear. It has been translated and validated into Persian, showing good reliability (ICC test-retest = 0.86) [65]. The MCID for individuals with chronic musculoskeletal pain is 4.5 points [66].

#### Adherence

The analysis will follow intention-to-treat (ITT) principles, including all patients based on randomization, regardless of whether they have received the primary interventions [37]. The principal investigator will document adherence to the exercise regimen in a weekly report. Moreover, missing data will be reviewed, and sensitivity analyses will be conducted when necessary. During the implementation period of the main intervention, weekly reminder calls and text messages will be sent to participants to remind them of the meetings [67,68].

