### Statistical analysis

The sample size has been estimated for the primary outcome of pain intensity (VAS), with emphasis on the proportion (%) of patients with improved CLBP on the VAS. The minimal important change in VAS is reported to be 15 mm [70]. Accordingly, we expect a minimal difference of 20% between the intervention groups in the proportion of patients with an improved VAS score (at least 15 mm) [27]. To detect a difference in main effects (i.e., PNE plus NMS vs NMS), the sample size calculation using G*Power software and like previous studies in the field of PNE (30), with an effect size difference of 0.25, an alpha value of 0.05 (two-sided test), and power (1 × b) 0.80, results in a required total sample size of 60 participants (30 patients per group). Assuming a dropout rate of 20%, we will enroll 30 patients per group.

A 2 × 2 variance analysis (treatment group × time) will be conducted using a mixed-model analysis design. The percentage change will be calculated for each variable compared to the baseline. The effect size (ES) using partial eta squared (ηp2) will be calculated to measure the clinical meaningfulness [71]. For ITT analyses, group means will replace missing data during the post-test. There will be no additional analyses (e.g., subgroup and adjusted analyses). All data analyses will be conducted using the SPSS software version 26 (IBM Corp., Armonk, NY, USA) at an alpha level of 0.05.

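### Missing-data sensitivity analyses are left to discretion and sit awkwardly with a ban on additional analyses, so no committed analysis tests the group-mean fill-in against pain-related dropout

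*Protocol article*

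**What the plan says.** Four statements in the protocol article bear on this.

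- **Adherence** adopts intention to treat: "The analysis will follow intention-to-treat (ITT) principles, including all patients based on randomization". It then says that "missing data will be reviewed, and sensitivity analyses will be conducted when necessary". No method, trigger or assumption to be tested is named.
- **Statistical analysis** fixes one way of handling missing values: "For ITT analyses, group means will replace missing data during the post-test". The next sentence reads "There will be no additional analyses (e.g., subgroup and adjusted analyses", closing the bracket there.
- **Statistical analysis** also expects appreciable loss: "Assuming a dropout rate of 20%, we will enroll 30 patients per group". That is 6 of 30 per arm.
- **Interventions: Concomitant care, modifications and adverse effects** lists, for patients in the intervention group, reasons for leaving that include "severe worsening of their clinical condition (e.g., presenting in a session with a VAS ranging from 8 to 10), they will discontinue the study". The VAS is the primary outcome measure.

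**The concern.** Replacing a missing value by the mean of the patient's own group assumes that those who leave resemble those who stay. The protocol itself names a route out of the study that contradicts this for the primary outcome: a patient who leaves because pain is high would be entered with the stayers' average. As worded, that route applies to the PNE plus NMS arm, so the error would favour the experimental treatment.

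A sensitivity analysis is the usual guard. Here it is optional, and the statistical section can be read as excluding it. Inspecting the observed data cannot show that the check is unnecessary, because the values that would settle the matter are the missing ones. A reader of the final report may therefore be unable to tell whether a favourable pain result would survive plausible values for the leavers.

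**Working it through.** **Inputs from the protocol article.** Dropout 20% and 30 patients per arm (Statistical analysis), so 6 leavers and 24 stayers per arm. Minimal clinically important difference 1.5 cm (Primary outcome, Pain). Fill-in by group mean (Statistical analysis), read here as the mean of the observed values in the patient's own arm.

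**Assumptions, not given in the article.** The excess pain d of leavers over stayers, taken as 1.5 cm and 3 cm. The SD of the pain comparison, taken as 2 cm and 3 cm. The article states no figure for missing-data bias, so there is none to reproduce.

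**Step 1: bias in one arm.** Let S be the stayers' mean. The true mean of all randomised patients in that arm is 0.8 × S + 0.2 × (S + d) = S + 0.2 × d. Group-mean replacement reports S. The arm's pain is understated by 0.2 × d:

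- d = 1.5 cm: 0.2 × 1.5 = 0.30 cm, which is 20% of 1.5 cm.
- d = 3 cm: 0.2 × 3 = 0.60 cm, which is 40% of 1.5 cm.

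**Step 2: bias in the arm difference.** With dropout proportions p and excesses d in the experimental (E) and control (C) arms, the bias is p_E × d_E − p_C × d_C.

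| Case | Bias in favour of PNE plus NMS |
|---|---|
| 20% in each arm, d = 1.5 cm in both | 0.30 − 0.30 = 0 |
| 20% in each arm, d = 1.5 cm in PNE plus NMS only | 0.30 cm |
| 20% in each arm, d = 3 cm in PNE plus NMS only | 0.60 cm |
| 30% v 10%, d = 1.5 cm in both | 0.45 − 0.15 = 0.30 cm |

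The bias needs a difference between arms, either in how many leave or in how unlike the stayers they are.

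**Step 3: what that bias does to a test with no true effect.** Take 24 v 24 observed values and a correct standard error, SE = SD × √(2/24). Two-sided 5% level, 46 degrees of freedom, noncentral t with noncentrality bias/SE:

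| SD (assumed) | SE | Bias 0 | Bias 0.30 cm | Bias 0.60 cm |
|---|---|---|---|---|
| 2 cm | 0.577 cm | 5% | 0.30/0.577 = 0.52 → 8.0% | 0.60/0.577 = 1.04 → 17.4% |
| 3 cm | 0.866 cm | 5% | 0.30/0.866 = 0.35 → 6.3% | 0.60/0.866 = 0.69 → 10.4% |

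The normal approximation gives 10.7% for the last cell, so about 10% to 11%. These rates isolate the bias from who leaves. They do not include the separate effect of single-value replacement on the standard error.

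**The case against.** **The two sections can be read together.** The examples given for excluded analyses are subgroup and adjusted analyses. These ask new questions or change the model. Re-running the primary comparison under another missing-data assumption is a different kind of analysis, and Adherence provides for it. This stands. A reader might infer that the statistical section forbids sensitivity analyses outright, but the text does not go that far. It leaves the matter unclear.

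**The details belong in a statistical analysis plan.** That is fair as regards method and shifts, and a plan not shown may supply them. It does not dispose of the point, because the article takes a position: it fixes group-mean replacement, makes the check optional and closes the list of analyses. A later plan would have to override some of that.

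**Reviewing missing data is not the same as seeing the results.** Correct. A reader might infer that the choice will be made after outcomes by arm are known. The article does not say so, and the amount and pattern of missingness can be reviewed blind. What stands is that nothing fixes the choice beforehand.

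**With 20% loss, the team would surely find a check necessary.** Possibly, but the article neither says so nor says what the check would be.

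**The error rates describe another problem.** Also correct. They belong to the primary test under informative dropout, rest on an assumed SD and on bias in one arm, and do not simulate the planned group-by-time analysis with filled-in values. A reader might infer that the missing sensitivity analysis itself raises the false-positive rate to 8% or 17%. It does not. A sensitivity analysis would leave the primary test as it is and disclose how fragile its result is.

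**Conclusion.** The point holds in a limited form. The article commits to a fill-in rule that treats leavers as average stayers, describes a route of exit linked to the primary outcome and worded for one arm, and commits to no analysis that would reveal the consequence. The conflict between Adherence and Statistical analysis is one of wording, but it should be resolved.

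The plausible size is 0.30 to 0.60 cm in favour of PNE plus NMS if leavers in that arm alone are 1.5 to 3 cm worse than its stayers, and nil if dropout and excess pain are equal in both arms. The corresponding false-positive rate of the primary test is about 8% to 17% at SD 2 cm and about 6% to 11% at SD 3 cm. The 20% dropout and the 1.5 cm yardstick are the article's own. The excess pain of leavers, its confinement to one arm and the SD are assumptions. It is also assumed that patients who discontinue provide no post-test value, which is the natural reading of leaving the study but is not spelled out.

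This should be changed. It does not invalidate the design.

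**What to change.** 1. In Adherence, replace 'when necessary' with a commitment, made before outcome data by arm are examined, to one delta-adjusted multiple-imputation (tipping-point) analysis of VAS at the 8-week post-test, and likewise at 6 months if that time point is analysed.
2. Take the zero-shift multiple-imputation result as the reference, not the group-mean result. Otherwise a change of method is mixed with a change of assumption.
3. Vary the shift added to imputed values separately in each arm over a stated grid, for example 0, 0.75, 1.5 and 3.0 cm (4 × 4 = 16 combinations). The grid then includes shifts in the PNE plus NMS arm only. Report the shift at which the conclusion changes.
4. In Statistical analysis, state that this analysis is excepted from the exclusion of additional analyses.

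The grid is one reasonable choice, tied to the article's 1.5 cm. Others would serve if fixed in advance. The cost is a second imputation model, a few sentences and one extra table. A positive result may be shown to be fragile. No clinical procedure changes.
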